## Country

Democratic Republic of Congo

## Site

Kikwit

**Version Protocol:**

September 18, 2012 (substantially)

15 August 2018 (slight reformatting, grammar errors corrected, one author margin comments was removed with its questions resolved).

**1. Introduction**

Typhoid Fever (TF) is a disease caused by the bacterium *Salmonella enterica* sv Typhi, which is contracted via faeco-oral transmission1. An inoculum as small as 100,000 organisms causes infection in more than 50% of healthy volunteers2. Humans are the only natural host and reservoir, and are infected through ingestion of faecally contaminated food or water. S. typhi may also be found in urine and vomitus of cases, and shellfish grown in sewage-contaminated water are potential vehicles, as are vegetables. Flies can mechanically transfer the organism to food, where the bacteria then multiply to achieve an infective dose. The highest incidence occurs where water supplies serving a large population are faecally contaminated. The incubation period is usually 8–14 days, but may range from 3 days up to 2 months. Some 2–5% of infected people become chronic carriers, who harbor *Salmonella* Typhi in the gall bladder. Chronic carriers are greatly involved in the spread of the disease3,4.

Clinical diagnosis of TF is challenging. In the absence of laboratory confirmation, any case of fever of at least 38 °C for 3 or more days is considered suspect if the epidemiological context is suggestive. Depending on the clinical setting and quality of available medical care, some 5– 10% of typhoid patients may develop serious complications, the most frequent being intestinal haemorrhage or peritonitis due to intestinal perforation.

An outbreak of TF has been recorded in Kikwit, Bandundu Province, in the Democratic Republic of Congo (DRC) in 2006 and 2011. Kikwit is the largest city of [Bandundu Province](http://en.wikipedia.org/wiki/Bandundu_(province)), lying on the [Kwilu River](http://en.wikipedia.org/wiki/Kwilu_River) in the southwestern part of the [Democratic Republic of Congo](http://en.wikipedia.org/wiki/Democratic_Republic_of_Congo). The population is approximately 350,000. Since the 2006 reported outbreak, TF has been endemic in Kikwit, with limited cases reported in 2009, 2010 and the 3 first trimestres of 2011.

Figure 1 shows the epidemic curve for Typhoid Fever cases from January 1, 2009 to December 31, 2011.

In week 46 of 2011, or five years after the first recorded outbreak, a second outbreak of TF occurred in Kikwit. Between November 14th and December 25th 2011, a total of 1438 cases were reported, of which 13 (1%) were confirmed by laboratory diagnosis: 6 were positive for *Salmonella* Typhi on 16 hemocultures and 7 were positive for *Salmonella* Typhi on 13 coprocultures. A total of 18 samples were rejected for analysis as not transported correctly. In total, 1367 simple TF cases and 71 cases with peritonitis and intestinal perforation were registered and approximately 22 patients have died (fatality rate 1,53 %).

Figure 2 shows the epidemic curve for the Typhoid Fever outbreak from November 14th until 25th December 2011.

Figures from the outbreak in 2006 and 2011 show an increase in cases of the disease at the beginning of the rainy season. Apart from this cyclic nature it can also be observed that in 2006 and 2011, the same geographic zones were systematically touched most; in these zones, a population of about 60,000 out of the 350,000 inhabitants of Kikwit are living. This information suggests that the TF outbreaks might be associated with a structural problem within a potential high TF risk zone in Kikwit. This hypothesis, that 7 out of the 33 “aires de santé” represent a hotspot of TF transmission within Kikwit, is currently the topic of a parallel focused investigation.

[figure not shown]

Figure 3: map of Kikwit Nord with hotspots of transmissions in 2006 and 2011 outbreaks

In Kikwit access to safe water is a challenge, and water source contamination is one of the most cited risk factors in a TF outbreak5. During the rainy season, where there is either no sewage disposal or working sewer system, runoff of rains follows the slopes down to the Lukemi River and contaminates open water sources used by the population of “Kikwit ville basse”, the lower lying part of town, with excreta. Even water produced at the borehole of Regisdeso at “Kikwit ville basse”, and sold to those who can afford it, might be contaminated. Chlorine is not adequately applied and as the water pressure in the outdated and leaking network is not constant, the contaminated surface water is sucked into the pipes the moment the pressure drops.

The central market, in proximity of this most affected “Kikwit ville basse” with its catastrophic hygienic circumstances, and the lack of knowledge in the population about the transmission process of TF, probably also compounds the propagation of the pathogen in the population.

In this study, we aim to investigate risk factors of TF transmission within a limited zone of Kikwit where TF transmission is particularly high in order to add to the growing evidence base on TF epidemiology.

**2. Aim and Objectives:**

Identify risk factors of TF transmission within a limited zone of Kikwit, where TF transmission was particularly high, in order to provide recommendations for future interventions against TF outbreaks in Kikwit and similar contexts.

**3. Methods**

3.1. Study Design:

A observational case-control study with individual matching for age and sex.

3.2. Setting:

Kikwit is the largest city of [Bandundu Province](http://en.wikipedia.org/wiki/Bandundu_(province)), lying on the [Kwilu River](http://en.wikipedia.org/wiki/Kwilu_River) in the southwestern part of the [DRC](http://en.wikipedia.org/wiki/Democratic_Republic_of_Congo). The population is approximately 350,000. The situation in DRC is dramatic in terms of health provision, with a weak health system, extremely poor accessibility of the existing health system and regular emergency levels of mortality figures, even in stable districts. These negative indicators are the result of, amongst others, decades of civil war and unrest, poor infrastructure and challenging geographical features, and poor management of the existing resources.

The sanitary district of Kikwit lies about 500 kilometers east of the capital, Kinshasa. It has a supervisee of 330 km² and a population density of approximately 1282 habitants per km². It is composed of 2 “zones de santé”:

- ZS de Kikwit Nord (161,046 habitants), 18 “aires de santé”, comprising 2 communes: Lukolela et Nzinda.
- ZS de Kikwit Sud (176,300 habitants), 15 “aires de santé”, comprising 2 communes: Lukeni et Kazamba

In Kikwit, the environment is mountainous with in the extreme north the river Kwilu. Between the different mountains exist small rivers and springs. Availability of potable water is challenging, especially in “Kikwit ville basse”, the lower lying part of Kikwit town. Piped water is too expensive for most of the population and its quality is compromised by inappropriate chlorination, and a leaking distribution network that allows aspiration of surface water when the pumps stop turning and the water pressure drops within the network. The price of the water also compromises its accessibility considerably. As a coping mechanism, the population uses open, unprotected springs to collect drinking water. Up to four or five springs can be identified per “aire de sante” and they well up at the bottom of the slopes in this mountainous environment. These sources are often situated close to small tributary rivers of the main river Kwilu. Only about 50 % of people in Kikwit own a latrine and wild defecation is rampant, also uphill of springs, leading to a high-risk environment for TF transmission. The central market of Kikwit also has an important potential to maintain TF transmission, with an absence of water and hand washing points on the market itself. Only one individual is responsible for cleanness in the market and most goods are presented on the ground instead of on tables. No latrines are available on the market.

3.3. Study site:

MSF is supporting Kikwit Nord General Hospital in order to offer free and quality treatment to simple TF patients as well as to those suffering from complications or perforation. Simple cases are given outpatient care and antibiotics, while complicated cases are hospitalized and perforated cases receive surgical treatment. MSF also provides medicines to the hospital, gives training to the personnel of the hospital and health centers around the city, and ensures that an adequate case definition and treatment protocol are implemented. Community workers are raising awareness among the population about basic hygiene practices, in order to halt this serious epidemic of TF, the so-called "dirty-hands disease”. These interventions are part of an emergency response, despite the fact that the problem is systemic and has repeated itself each 5 years in Kikwit.

## 3.4. Study population

The study population consisted of TF cases randomly selected from the line list of cases who are living within 7 out of the 33 “aires de santé”, believed to be hotspots of TF transmission within Kikwit.

The case definition during the outbreak was provided jointly by the Ministry of Health and the World Health Organization. A **Suspected case** is any person with gradual onset of steadily increasing and then persistently high fever, malaise, headache, sore throat, cough, and, sometimes, abdominal pain and constipation or diarrhea. A **Confirmed case** is asuspected case confirmed by isolation of *Salmonella* Typhi from blood, bone marrow, duodenal fluid or stool. For the confirmation of TF, isolation of *Salmonella* Typhi is required. Blood culture is the mainstay of the diagnosis. In endemic areas, stool isolation alone is insufficient for diagnosis if the clinical picture is not complete.

Two controls of the same sex, age class (10 to 14, 15 to 19, 20 to 29, 30 to 39, 40 to 49 and more than 50) and “aire de santé” will be selected per case. Selection criteria for controls are not having been suspected of TF during the study period and having the possibility to present themselves at the health structure during the study period if required.

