## 3.6. Sampling procedure

A representative sample of cases will be selected by random sampling, using random numbers generated in MS Excel, from a line list of cases who are living within the 7 “aires de santé” believed to be hotspots of TF transmission within Kikwit. Controls will be selected in two phases.

In the first phase, a geo-referenced polygon around each of the the 7 “aires de sante” will be generated from images obtained from Google Earth. Then with the help of the software package R, a total of 1500 random points will be generated within this polygon and the geographic coordinates of each point will be registered. Again, with the help of Google Earth images, all the points not falling on the roof of a house will be eliminated. Finally, 640 houses will be selected at random from the remaining points and allocated to cases: the first and the second point will be allocated to case 1, the third and fourth to case 2, and so on. As such, each case of the study population will have 2 random points allocated that each correspond to a house within the polygon.

In the second phase, with the help of a GPS, the corresponding houses will be visited by field teams. Within the household, a control will be recruited, matching the corresponding case in sex and age, and without suspicion of TF during the study period. If within this household no one matches the case or no one corresponds to the control criteria, then the field team will survey the next occupied building to the right. A household is defined as a group of people sleeping in the house and sharing the meals regularly during the study period.

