## 3.7. Study period

## This case control survey will be carried out in Kikwit between November 2012 and February 2013 and is related to the TF outbreak that struck Kikwit between November 14th and December 25th 2011.

## 3.8. Study procedures

A semi-structured questionnaire was developed to gather information on the presence or absence of TF morbidity in conjunction with various factors (basic socio-demographics; water source/s, storage capacity, and point-of-use treatment; hygiene and sanitation practices; food and drink consumption; and health seeking behavior). The number of questions was limited to be amenable. The survey questionnaire is provided as Annex I. Information was collected both at the level of individual respondent and of each household as a whole. On consultation with national staff, the minimum age for respondents was set at 10 years.

The questionnaire was translated from English to French, back-translated by a second translator for verification, and piloted in an area of Kikwit not included in the selected sample. The survey team will comprise of residents of Kikwit (both men and women), coordinated by supervisors. The supervisors will control the quality of completed forms and data entry, and additional random checks will be carried out by the survey coordinator.

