3.9. Sources of data

Sources of data are as follows: official data from the Ministry of Health registers (line list) will be used to describe the previous epidemics in terms of person, time and place. This line list has been created by the MOH in order to register every suspected case of TF, and contains several items of interest such as name, address, sex, age, date of onset, date of admission, symptoms at admission, status, results of laboratory analysis and outcome.

Population data (denominators) used for rate estimations will be obtained from the census bureau in Kikwit.

Complementary sources of information will be:

- interviews with the health authorities of the concerned area.
- environmental evaluations in the most affected area’s.
- visit to the reference hospital.
- visit to the reference laboratory.
- chemical and biological water tests.

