## 3.13. Data and statistical analysis

Questionnaire results will be encoded in full. Data will be processed and analysed (bivariate and multivariate analysis) using Epi-Info and STATA software packages. For all individual variables, results will be analyzed as three groups, respondents contracting simple, complicated or no TF during the 2011 outbreak.

4. Ethics issues:

The general medical and sanitation activities during the Kikwit Typhoid Fever outbreak response were part of the overall MSF emergency response and were in line with standard MSF conduct. General measures were in place to ensure confidentiality and support for all patients, as is standard MSF practice, and these measures will also be respected while conducting the survey. All care provided to the patients was free of charge, as standard for MSF. Data included in this analysis will not include patient identifiers. The nature and purpose of the survey will be explained to each household and verbal consent will be obtained from every individual prior to survey administration. Ethical approval will be sought from the Ethics Review Boards of MSF and the Ministry of Health of DRC in order to perform the analysis of the survey in full compliance with the ethical requirements within DRC and MSF.

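### A case-control difference in health-seeking behaviour cannot be read as a typhoid risk factor, because cases enter through a register that implies contact with care and controls do not

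*Protocol*

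**What the plan says.** **Cases.** Protocol section 3.4 takes "TF cases randomly selected from the line list of cases who are living within 7 out of the 33" health areas. Section 3.9 explains the register: "This line list has been created by the MOH in order to register every suspected case of TF". Its fields include "date of onset, date of admission, symptoms at admission, status, results of laboratory analysis and outcome".

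**Controls.** Under section 3.6, "640 houses will be selected at random from the remaining points and allocated to cases", with the next occupied building to the right used if nobody in the house qualifies. Section 3.4 adds: "Selection criteria for controls are not having been suspected of TF during the study period and having the possibility to present themselves at the health" facility in the study period, should that be needed. Section 3.4 also matches controls on sex, age class and health area.

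**Period.** Section 3.7, headed as the study period, dates the survey to November 2012 to February 2013 and says it relates to the outbreak of 14 November to 25 December 2011.

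**Variables and analysis.** Section 3.8 lists among the factors gathered "hygiene and sanitation practices; food and drink consumption; and health seeking behavior". Section 3.12 describes the study's focus as demographics, water, hygiene and food or drink, without naming health-seeking. Section 3.13 states: "For all individual variables, results will be analyzed as three groups, respondents contracting simple, complicated or no TF during the 2011 outbreak". No section exempts health-seeking from that comparison.

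**The concern.** In a case-control study, controls should be people who would have become study cases had they fallen ill. Here, becoming a case takes two steps: having the illness and being entered on the line list. The admission fields suggest that the second step ran through a health structure. A control passes no comparable step. The access criterion concerns ability to attend, not whether the person would have gone, and it may refer to the survey months rather than the outbreak.

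For most exposures this matters only indirectly. For health-seeking behaviour it matters directly, because the variable is itself a determinant of registration. The stated aim is to recommend interventions, so an association created by registration could be reported as a risk factor and acted on. Control screening questions cannot be added once fieldwork is over.

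**Working it through.** **1. The plan's own figure.** Section 3.5 gives an odds ratio of 1.5, 30% exposure in controls, 80% power and two controls per case. Alpha is not stated; 5% two-sided is assumed.

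- Case exposure: 1.5 × 0.30 / (0.70 + 1.5 × 0.30) = 0.45 / 1.15 = 0.391.
- The unmatched two-proportion formula gives 316 cases and 632 controls, against the stated 320 and 640. Power at 320 and 640 is 80.5%.

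The sample size reproduces, so these numbers serve as a yardstick.

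**2. Health-seeking itself.** Let q be the proportion of care-seekers in the source population. Suppose care-seeking has no effect on typhoid, and ill seekers and non-seekers are registered with probabilities r₁ and r₀.

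- Odds of care-seeking among cases: [q / (1 − q)] × (r₁ / r₀).
- Odds among controls: q / (1 − q).
- Expected odds ratio: r₁ / r₀, whatever q is.

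The protocol gives neither q nor r₁ / r₀, so both are assumed over a range. The table shows the chance of a significant result (two-sided 5%, 320 cases, 640 controls) for a factor with no true effect.

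| r₁ / r₀ | Expected OR | q = 30% | q = 50% | q = 70% |
|---|---|---|---|---|
| 1 | 1 | 5% | 5% | 5% |
| 1.25 | 1.25 | 34% | 37% | 30% |
| 1.5 | 1.5 | 80% | 84% | 73% |
| 2 | 2 | 99.8% | 99.9% | 99% |

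**3. Spill-over to other exposures.** Suppose half the source population would seek care, only seekers are registered, and a null factor has 30% prevalence overall. The expected odds ratio is odds(prevalence in seekers) / odds(0.30).

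- 25% in seekers, 35% in non-seekers: 0.333 / 0.429 = 0.78.
- 20% in seekers, 40% in non-seekers: 0.250 / 0.429 = 0.58.

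These figures give no credit to the access criterion, area matching or free care, so they illustrate an unfavourable case.

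**4. Unregistered illness among controls.** The 1438 reported cases are for Kikwit as a whole. Dividing by the roughly 60,000 residents of the most affected zones gives at most 2.4%. If unregistered illness were 1 to 4 times that (assumed) and none of it were screened out, c = 0.024 to 0.096, or 15 to 61 of 640 controls. Control exposure becomes (1 − c) × 0.30 + c × 0.391 = 0.302 to 0.309, and a true odds ratio of 1.5 appears as 1.48 to 1.44. This is minor.

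**The case against.** Several stronger readings are tempting, and the protocol does not support them.

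- **That cases could enter only by seeking care.** Section 3.9 says the list was meant to register every suspected case and does not say how cases were found. The admission fields make facility contact likely; they do not exclude active finding.
- **That controls come from all houses without restriction.** Section 3.4 has an access criterion. It is weak, but it exists.
- **That anyone ill at home is a valid control.** Section 3.4 defines a suspected case by symptoms, with no consultation required, and section 3.8 asks about typhoid morbidity. Such a person may already be excluded. Annex I, which would settle this, is not among the material available.
- **That any odds ratio for health-seeking is pure artefact.** The bias depends on an unknown registration ratio and on how the items are worded. The simple-versus-complicated contrast lies within registered cases and does not cross the two selection routes.
- **That wealth, distance and paid-for water are distorted to the same degree.** Matching on health area limits differences in distance, and treatment was free (sections 3.3 and 4), which weakens the wealth route. The phrase "extremely poor accessibility of the existing health system" in section 3.2 describes the country, not Kikwit during the supported response.

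It can also be said that section 3.12 leaves health-seeking out of the study's focus. That lowers the stakes, but section 3.13 still covers all individual variables. What stands against the objection is narrow: registration probably depends on care contact, the control criteria do not equalise it, and the affected comparison is planned.

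Making the main analysis depend on controls who say they would have used a registering structure would cost too much. If half qualified, 320 controls would remain and unmatched power would fall from 80.5% to about 68%.

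**Conclusion.** The point holds in a limited form. A case-versus-control difference in health-seeking behaviour cannot be interpreted as a typhoid risk factor under this design. The water, hygiene and food comparisons are affected only to the extent that those exposures go with care-seeking, and area matching, free care and the access criterion partly contain that.

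The size of the bias cannot be determined from the protocol. Under the assumption of no true effect, a registration ratio of 1.5 is enough to produce an odds ratio of 1.5, and a ratio of 1 produces none. Contamination of controls is a secondary matter even on assumptions that ignore all screening. The conclusion rests on one inference, that registration ran mainly through contact with a health structure. It is an inexpensive improvement to the plan and does not invalidate the study's main comparisons.

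**What to change.** 1. **Section 3.13:** exclude health-seeking behaviour from the case-control risk-factor analysis and report it descriptively. The simple-versus-complicated contrast among registered cases may stay.
2. **Sections 3.4 and 3.6:** state that the control criteria refer to 14 November to 25 December 2011. At screening, ask each control whether they had a prolonged fever in that window (section 1 uses at least 38 °C for 3 or more days) and where they would have sought care for it.
3. **Section 3.13:** keep all eligible controls in the main analysis. Add two sensitivity analyses, one excluding controls who report such a fever and one restricted to controls who would have used a structure that fed the line list.

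The cost is a few sentences and two screening questions. Both questions rely on recall about a year after the event, and the second is hypothetical. Power falls in the sensitivity analyses only; the main analysis keeps its planned 320 cases and 640 controls.

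### Control eligibility is tied to a study period whose only stated dates are those of the 2012-13 survey, while TF status is analysed for the 2011 outbreak; the window should be dated explicitly

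*Protocol*

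**What the plan says.** Four places in the protocol bear on the time window.

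- **Section 3.4 (Study population)**, on controls: "Selection criteria for controls are not having been suspected of TF during the study period". They must also have been able to present at the health structure in that same, undated period.
- **Section 3.6 (Sampling procedure)** repeats the rule for the field teams, who recruit a control "matching the corresponding case in sex and age, and without suspicion of TF during the study period". It also defines the household by that period: "A household is defined as a group of people sleeping in the house and sharing the meals regularly during the study period".
- **Section 3.7 (Study period)**, the only section under that heading: "This case control survey will be carried out in Kikwit between November 2012 and February 2013". The same sentence adds that the survey "is related to the TF outbreak that struck Kikwit between November 14th and December 25th 2011".
- **Section 3.13 (Data and statistical analysis)** forms three groups: "respondents contracting simple, complicated or no TF during the 2011 outbreak".

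Nothing in the protocol says that a person suspected of TF in the 2011 outbreak cannot be a control. Nothing requires a control to have lived in the aire de santé at the time of that outbreak.

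**The concern.** In a case-control study the controls should come from the population that produced the cases, over the same window. Here the analysis concerns illness in November and December 2011, but the term that sets control eligibility is dated about a year later. If a field team applies section 3.7 literally:

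1. a person suspected of TF in 2011, and not again in 2012-13, can be recruited as a control;
2. a person who moved into the aire de santé after December 2011 can be recruited, although not part of its population during the outbreak;
3. a person free of TF in 2011 but first suspected in 2012-13 is turned away, although a proper control for the 2011 outbreak. The Introduction describes TF as endemic since 2006, so this can happen.

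What is at stake is whether the reference group matches the label that section 3.13 gives it, and whether the individually matched sets of section 3.1 survive into the analysis.

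**Working it through.** **The windows side by side**

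| Item | Section | Window |
|---|---|---|
| No suspected TF (controls) | 3.4, 3.6 | study period, undated |
| Able to attend the health structure (controls) | 3.4 | study period, undated |
| Study period | 3.7 | November 2012 to February 2013 |
| Outbreak the survey relates to | 3.7 | 14 November to 25 December 2011 |
| TF status in the analysis | 3.13 | 2011 outbreak |

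Eligibility and analysis coincide only if the reader replaces the dates that section 3.7 gives for the survey with those it gives for the outbreak. The literal reading is also awkward in the field: a control interviewed in November 2012 cannot yet meet a condition that runs to February 2013.

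**The plan's own sample size.** Inputs from section 3.5: odds ratio 1.5, control exposure p0 = 0.30, power 80%, two controls per case. Alpha is not stated; 0.05 two-sided is assumed.

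- Case odds of exposure: 1.5 × 0.30/0.70 = 0.6429, so p1 = 0.6429/1.6429 = 0.3913.
- Pooled exposure: (0.3913 + 2 × 0.30)/3 = 0.3304.
- n = [1.96 × √(1.5 × 0.3304 × 0.6696) + 0.84 × √(0.3913 × 0.6087 + 0.30 × 0.70/2)]² / (0.3913 − 0.30)², which gives 316 cases.

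The protocol has 320 cases and 640 controls, so its figure is reproduced to within 3%. Power at 320/640 is 80.5%.

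**Reported 2011 cases entering as controls.** The Introduction says of the outbreak that "a total of 1438 cases were reported", and that in the most affected zones "a population of about 60,000 out of the 350,000 inhabitants of Kikwit are living". Let c be the share of controls who are former cases. Assume that they have the exposure of cases and that all other controls have 30%:

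- control exposure = 0.30 + c × (0.3913 − 0.30)
- observed odds ratio = 0.6429 / (odds of that exposure)

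| Assumption on where reported cases lived | c | Former cases among 640 | Control exposure | Odds ratio | Power |
|---|---|---|---|---|---|
| None enter as controls | 0 | 0 | 0.3000 | 1.500 | 80.5% |
| Spread over the city (1438/350,000) | 0.41% | about 3 | 0.3004 | 1.497 | 80.2% |
| All in the hotspot (1438/60,000) | 2.40% | about 15 | 0.3022 | 1.484 | 78.6% |

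The last row is the upper limit for reported cases, because the 1438 are not stated to be confined to the hotspot. It averages over all ages; the protocol gives no age-specific counts from which to refine it for the matched age classes.

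**Post-outbreak arrivals.** The protocol gives neither the share of arrivals nor their exposure. No figure can be computed, and the direction of any bias depends on that unknown exposure.

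**The case against.** The best defence is that the text, read as a whole, means the 2011 outbreak. Section 3.7 names both windows in one sentence, the control criterion is phrased in the past, and section 3.13 speaks of the 2011 outbreak. Sections 3.4 and 3.6 do not date the cases either: the reader takes 2011 for them from context, and the same context is available for controls. This stands as evidence of intent. It does not remove the defect, because field teams screen house by house on the written rule, and the only section that explains the term opens with the survey dates.

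A second defence is that TF status is collected anyway. Section 3.8 says that the questionnaire records TF morbidity, and section 3.9 says that the line list holds names and addresses. A recruited control who reports TF in 2011 could therefore be moved out of the no-TF group. That limits contamination, but the move breaks the matched set after recruitment. The questionnaire annex is not in the text at hand, so how well it would detect such people cannot be judged.

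Three stronger readings might be inferred, and the protocol does not support them.

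- **Large attenuation.** If 10% or 20% of controls had had TF in the outbreak, the same formula gives odds ratios of 1.44 or 1.38. Those shares have no basis in the protocol and would consist mainly of illness that was never suspected. Such people would remain eligible after the dates are corrected, so this is a separate question of misclassification.
- **Arrivals bias odds ratios towards 1 and were never at risk.** The direction is unknown, and someone who moved within Kikwit may well have been at risk, since the Introduction calls the hotspot zones the most affected, not the only ones.
- **The household definition must also be set back to 2011.** Receptacles and latrines are inspected and water is sampled at the survey (sections 3.8 and 3.10), so current membership is a sensible meaning there.

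**Conclusion.** The point holds as a badly fixed definition that should be corrected. Sections 3.4 and 3.6 rest control eligibility on a term that section 3.7 dates to the survey, whereas section 3.13 analyses the 2011 outbreak. The outbreak was probably intended, so it cannot be said that 2011 cases will in fact be recruited as controls, only that the rule as written permits it.

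For reported cases the size is small: at most about 2.4% of controls, an odds ratio of 1.48 in place of 1.50, and power of 78.6% in place of 80.5%. This assumes two-sided alpha of 0.05, an unmatched approximation, all reported cases resident in the hotspot, and former cases with the exposure of cases. The effect of post-outbreak arrivals cannot be sized or signed. The reason to act is therefore that the control group should be guaranteed to come from the population and time that gave rise to the cases; the numerical loss alone would not require it.

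**What to change.** - **Section 3.7:** call November 2012 to February 2013 the survey period, and state 14 November to 25 December 2011 as the outbreak window.
- **Sections 3.4 and 3.6:** require that a control had no suspected TF in the outbreak window, checked against the line list; lived in the same aire de santé in that window; and could have attended the health structure then.
- **Age class:** fix it at November 2011 for cases and controls alike, since line-list ages date from the outbreak and controls are met about a year later.
- **Household definition in section 3.6:** keep it as current membership, worded as at the survey. The separate residence criterion does what is needed for eligibility.

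The planned 320 cases and 640 controls do not change. The cost is revised wording, a residence question and a line-list check at recruitment, and a few more substitutions to the next house where the occupants arrived after the outbreak.
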